## Abstract

**Background:**

It is controversial whether or not the carpometacarpal joint (CMCJ) should be included in total wrist arthrodesis (TWA). Complications commonly occur at this site and studies examining its inclusion and exclusion are conflicting. A randomised clinical trial comparing wrist arthrodesis with CMCJ arthrodesis and spanning plate to wrist arthrodesis with CMCJ preservation and non-CMCJ spanning plate has not been performed.

**Method:**

A single centre randomised clinical trial including 120 adults with end-stage isolated wrist arthritis will be performed to compare TWA with and without the CMCJ included in the arthrodesis. The primary outcome is complications in the first post-operative year. Secondary outcomes are Disabilities of the Arm, Shoulder and Hand (DASH) score, Patient Rated Wrist Evaluation (PRWE) and grip strength measured at 1, 2 and 5 years. Late complications, return to work and satisfaction will also be recorded.

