The advantages of preserving the CMCJ in TWA is that a small amount of motion is preserved in the hand. Seven degrees of flexion/extension, 4 degrees of radio-ulna deviation and 5 degrees of pronation-supination is present in the native third CMCJ [13], which is most commonly fused in TWA. Motion at the CMCJ improves grip strength and the ability to make a fist. Disadvantages of preservation of the CMCJ in TWA are that hypermobility and pain may develop after TWA without CMCJ arthrodesis, which may be explained by increased loading of the CMCJ though an immobile wrist. It is hypothesised that this may cause accelerated degeneration of this joint and pain after TWA.

The total wrist arthrodesis with and without arthrodesis of the carpometacarpal joint study (WAWWAM study) is a single centre, multi-surgeon triple blinded randomised trial that will examine the outcome of two different treatments of the CMCJ in TWA.

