### Baseline data

A timeline for assessment is given in Fig. 1. Initial pre-operative assessment will obtain data on comorbidities, function, clinical assessment of pain at the CMCJ and radiographic assessment with x-ray and computer tomography (CT). Patient reported outcome measures including the DASH and the PRWE will also be administered.

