### Secondary outcomes

Secondary outcomes will include changes from baseline DASH and PRWE. Secondary outcomes will also include patient satisfaction, grip strength and late complications.

The DASH questionnaire is used to assess global disability of the upper limb. The questionnaire is a self-reported 30 item questionnaire that patients rate difficulty and interference with daily life on a 5-point Likert scale. The DASH is scored using the formula = ([(sum of n responses)/n] -1) where n represents the number of completed items. The score on both test ranges from 0 (no disability) to 100 (most severe disability).

The PRWE is a wrist specific questionnaire that has 15-items designed to measure wrist pain and disability in activities of daily living. The pain subscale contains 5 items each of which is further rated from 1 to 10. The function subscale contains a total of 10 items which are further divided into 2 sections: specific activities (6 items) and usual activities (4 items). Both subscales are scored out of 50, and the total score is the sum of the two scores, where 100 is the poorest possible outcome.

Grip strength will be recorded from three attempts alternating between left and right hands have using Jamar digital dynamometer in position 2.

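### The protocol text names no pre-operative grip strength measurement and no baseline adjustment for grip, so the grip comparison may lose precision and change in grip may not be reportable

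*Protocol article*

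**What the plan says.** The abstract (Method) groups three secondary measures under one set of times, ending with "grip strength measured at 1, 2 and 5 years"; DASH and PRWE precede grip in the same list.

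Baseline data describes what is collected before surgery. The clinical and imaging part reads "Initial pre-operative assessment will obtain data on comorbidities, function, clinical assessment of pain at the CMCJ and radiographic assessment", by x-ray and CT. The patient-reported part reads "Patient reported outcome measures including the DASH and the PRWE will also be administered". Grip strength is not named in either.

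Secondary outcomes makes the same split. One sentence reads "Secondary outcomes will include changes from baseline DASH and PRWE". The next reads "Secondary outcomes will also include patient satisfaction, grip strength and late complications", with no reference to baseline. The measurement itself is described: "Grip strength will be recorded from three attempts alternating between left and right hands", with a Jamar digital dynamometer in position 2. No time point is attached to it there.

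The Background links grip to the treatment question: "Motion at the CMCJ improves grip strength and the ability to make a fist". The Objectives list function and grip strength as separate clinical outcomes. Statistical analysis assigns continuous secondary outcomes to ANOVA and names no covariate.

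**The concern.** Grip is the objective measure of one of the benefits that the protocol attributes to leaving the carpometacarpal joint unfused. Of the three secondary measures named in the abstract, two appear by name in the pre-operative assessment and the third does not.

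If grip is first measured at one year, two things are lost. Change from the pre-operative state cannot be reported, and differences between patients in starting strength stay in the residual variance when they could have been removed by adjustment. The pre-operative value cannot be recovered once the wrist has been fused, so a late correction does not help patients already operated on.

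**Working it through.** **Where grip appears in the text**

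| Place | DASH and PRWE | Grip strength |
|---|---|---|
| Abstract, Method | 1, 2 and 5 years | 1, 2 and 5 years |
| Baseline data | named | not named |
| Secondary outcomes | change from baseline | listed, no baseline reference |
| Statistical analysis | ANOVA, no covariate named | ANOVA, no covariate named |

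The abstract row settles nothing alone, because DASH and PRWE carry the same times and do have a baseline. The point rests on the second and third rows.

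**Inputs for the size of the loss**

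- Total of 120, dropout 20%, alpha 0.05, power 0.80 (Sample size). Whether alpha is one- or two-sided is not stated; two-sided is assumed here.
- Allocation 1:1 (Randomisation and blinding).
- The correlation r between pre-operative and follow-up grip is not given. It is assumed and shown as a range.
- The SD of grip is not given, so results are in SD units.

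The total of 120 was set for carpometacarpal complications and no event rates are stated, so it cannot be reproduced. It is used only to obtain the evaluable number: 120 × (1 − 0.20) = 96, or 48 per arm.

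**Follow-up values only**

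Standard error of the difference = √(2/48) = 0.204 SD. Detectable difference = (1.960 + 0.842) × 0.204 = 0.572 SD.

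**With pre-operative grip as an ANCOVA covariate**

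The residual SD is multiplied by √(1 − r²), and so is the detectable difference. The variance falls by r². Power is shown for an illustrative true difference of 0.5 SD.

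| Assumed r | √(1 − r²) | Detectable difference (SD) | Variance reduction | Power at 0.5 SD |
|---|---|---|---|---|
| no adjustment | 1 | 0.572 | 0% | 68.8% |
| 0.2 | 0.980 | 0.560 | 4% | 70.5% |
| 0.3 | 0.954 | 0.546 | 9% | 72.8% |
| 0.5 | 0.866 | 0.495 | 25% | 80.7% |
| 0.7 | 0.714 | 0.408 | 49% | 92.9% |

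**Why ANCOVA and not a simple change score**

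The variance of a change score, relative to the follow-up value, is 2(1 − r): 1.6 at r = 0.2, 1.4 at 0.3, 1.0 at 0.5 and 0.6 at 0.7. A change score is less precise than the raw follow-up value whenever r is below 0.5. ANCOVA does better than the raw value at every r in the table.

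**The case against.** The strongest reply is that an article's silence is being read as a design decision. The assessment timeline is in Fig. 1 and the pre-operative forms are in additional files, neither of which was available for this review, and those are the natural places for a baseline item list. Baseline data also lists function without defining it. This stands in part. The Objectives list function and grip as separate items, which weakens the reading that one includes the other but does not exclude it. A reader might infer from the abstract that grip is scheduled only after surgery and that the trial has no baseline grip. The documents do not support that: the same phrase covers two measures that do have a baseline.

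A second reply concerns harm. A reader might infer that chance imbalance in starting strength biases the grip comparison. It does not. Allocation is randomised 1:1, and chance imbalance is already reflected in the standard error. Only precision and the reporting of change are affected. Both hands are measured, so contralateral grip could recover part of the precision. The gains tabulated above are against no adjustment at all and would be smaller against contralateral adjustment. Contralateral grip does not, however, give change from the pre-operative state.

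Third, the correlation is not in the document. Pre-operative grip is taken in a wrist with end-stage arthritis, before an operation meant to eliminate pain, so a low correlation is plausible. At r = 0.2 the gain is negligible.

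Finally, the choice of covariates is commonly left to the analysis plan, which was not available. That is fair for the model alone, but no analysis plan can supply a pre-operative value that was never measured.

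**Conclusion.** The point holds in a limited form. The text never places grip strength before surgery, although it gives better grip as a benefit of preserving the joint, and the analysis it names has no baseline adjustment. Whether grip is in fact measured pre-operatively cannot be settled from the text.

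If it is not measured, the comparison remains valid but less precise than it could be. The detectable difference is about 0.57 SD, where adjustment would give between 0.56 SD (r = 0.2) and 0.41 SD (r = 0.7). These figures assume 48 evaluable patients per arm, two-sided 0.05, 80% power and a normal approximation, and the size of the gain depends wholly on the assumed correlation. If grip is measured, the same gain is available at no measurement cost by using it as a covariate.

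Severity is low: grip is one of several secondary outcomes and the sample size does not rest on it.

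**What to change.** 1. Check Fig. 1 and the pre-operative form. If grip is there, name it in Baseline data and add baseline to the grip times in the abstract.
2. If it is not there, add it before randomisation by the method already described in Secondary outcomes (same device and position, three alternating attempts, both hands), and state it in Baseline data.
3. In Statistical analysis, specify ANCOVA for grip with pre-operative grip of the operated side as covariate. Where that value is missing, for example in patients operated on before the change, use contralateral grip. If this is taken at follow-up, it rests on the assumption that allocation does not affect the other hand.

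The cost is a few minutes per patient with equipment the trial already uses, at an assessment that already takes place, plus one line on the form. If grip is already collected, the cost is only the wording.

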**Discussion:**

It is unknown whether the CMCJ should be included in TWA. This trial will contribute to an improved understanding of optimal management of the CMCJ in total wrist arthrodesis.

**Trial registration:**

This trial was prospectively registered with the Australia New Zealand Clinical Trials Registry with identifying number ACTRN12621000169842 on the 16th February 2021.

WHO: U1111–12626523.

ANZCTR:

ACTRN12621000169842

**Supplementary Information:**

The online version contains supplementary material available at 10.1186/s12891-021-04644-4.

## Background

Total wrist arthrodesis (TWA) is indicated for a variety of wrist conditions where motion preserving procedures are contraindicated [1]. The aim of TWA is to eliminate pain and provide stability to improve function [2]. TWA with a dorsal contoured wrist arthrodesis plate has been widely adopted [3–9]. Complications of TWA with a plate include non-union, soft tissue irritation and hardware failure. The carpometacarpal joint is a common site of complications [4, 10, 11].

Inclusion of the carpometacarpal joint in TWA is debated and complications at this site are mentioned throughout the literature [2]. Early descriptions of TWA using a plate mandated inclusion of the carpometacarpal joint. Inclusion of this joint is recommended, as persistent loading of the plate across a mobile joint may result in plate failure, and to prevent this plate removal is recommended. Arthrodesis of the CMCJ at the time of TWA is indicated for localised pain or degeneration of the joint. Some authors recommend routinely including the CMCJ in TWA, while others recommend arthrodesis for heavy manual workers.

Nagy recommended against CMCJ arthrodesis noting a high frequency of non-union and pain in patients that had hardware removed [10]. In a similar study, Berling disagreed, instead preferring to fuse the carpometacarpal joint to reduce the requirement for plate removal with a second operation [11]. Rancy compared a non-carpometacarpal spanning plate to a spanning plate with carpometacarpal joint fusion in a small retrospective series and reported similar results for both treatment groups [12]. Most recently, Hernekamp compared the Medartis APTUS© 2.5 TriLock Wrist Fusion Plate, which is a specially designed non-spanning plate that enables the carpometacarpal joint to be spared to the Depuy-Synthes© CMCJ spanning LCP wrist fusion plate without CMCJ arthrodesis, reporting similar results [4].

The advantages of preserving the CMCJ in TWA is that a small amount of motion is preserved in the hand. Seven degrees of flexion/extension, 4 degrees of radio-ulna deviation and 5 degrees of pronation-supination is present in the native third CMCJ [13], which is most commonly fused in TWA. Motion at the CMCJ improves grip strength and the ability to make a fist. Disadvantages of preservation of the CMCJ in TWA are that hypermobility and pain may develop after TWA without CMCJ arthrodesis, which may be explained by increased loading of the CMCJ though an immobile wrist. It is hypothesised that this may cause accelerated degeneration of this joint and pain after TWA.

The total wrist arthrodesis with and without arthrodesis of the carpometacarpal joint study (WAWWAM study) is a single centre, multi-surgeon triple blinded randomised trial that will examine the outcome of two different treatments of the CMCJ in TWA.

### Objectives

The aim of this study is to compare the outcomes of TWA with a CMCJ spanning plate and CMCJ arthrodesis to TWA with a non-spanning plate without CMCJ arthrodesis.

Specific aims:
To compare perioperative and short-term (up to 12 months) complicationsTo compare clinical outcomes: pain, satisfaction, return to work, function, grip strengthTo compare long-term (1–5 years) complications and CMCJ problemsTo compare patient reported outcomes: Disabilities of Arm, Shoulder, Hand (DASH) and Patient Rate Wrist Evaluation (PRWE)

## Methods/design

### Trial design

This study is a single centre randomised trial. It has a parallel group design and is stratified by surgeon. Trial admission and randomisation will occur preoperatively.

### Ethics

Approval for the conduct of this study has been received from the Australian Capital Territory Health (ACT) Services Directorate Human Ethics Committee: 2020.ETH.00207.

### Participants

Adults aged 18 years and older awaiting TWA will be invited to participate in this trial. Participants will be English speaking, have minimal disability of the upper limb and have non-inflammatory arthritis of the wrist. Additional eligibility criteria are specified in Table 1. The CONSORT statement is followed for the reporting of randomised trials. A participant’s journey through the trial is shown in Fig. 1.

**Table 1 Tab1:** Eligibility and exclusion criteria

Eligibility criteria	
Inclusion criteria	
This study will include English speaking adults aged > 18 years who have been scheduled for total wrist arthrodesis. The conditions which are likely to be included are:	
SNAC (Scaphoid non-union advanced collapse)	
SLAC (Scapholunate ligament advanced collapse)	
Keinbock’s disease/Lunate avascular necrosis	
Preiser’s disease/Scaphoid avascular necrosis	
Wrist osteoarthritis	
Post traumatic arthritis	
Failed partial fusion	
Failed proximal row carpectomy	
Failed ligament repairs	
Exclusion criteria	
Patients will be excluded from this study if they:	
Lack ability to provide informed consent for participation (cognitive capacity or English proficiency)	
Have an inflammatory arthropathy (e.g., Rheumatoid arthritis)	
Have coexisting debilitating other upper limb disorder e.g., rotator cuff tear arthropathy with inability to raise arm above head.	
Neurological dysfunction affecting the limb of interest (CVA, plexus injury, peripheral nerve injury, spasm or contracture)	
Tumour of the wrist (giant cell or other)	
Wrist arthroplasty that will be revised to arthrodesis	
Planned to undergo or have undergone bilateral wrist arthrodesis

**Fig. 1 Fig1:**
[figure not shown]
SPIRIT timeline for trial

### Baseline data

A timeline for assessment is given in Fig. 1. Initial pre-operative assessment will obtain data on comorbidities, function, clinical assessment of pain at the CMCJ and radiographic assessment with x-ray and computer tomography (CT). Patient reported outcome measures including the DASH and the PRWE will also be administered.

### Randomisation and blinding

Block randomisation with stratification by surgeon will be used to ensure equal distribution of participants and size of each treatment group in the event that recruitment goals are not achieved. Eligible patients are randomised 1:1 to TWA with CMCJ arthrodesis and spanning plate or TWA without CMCJ arthrodesis with non-CMCJ spanning plate. The randomisation sequence is concealed and administered by an independent non-clinical staff member of the Trauma and Orthopaedic Research Unit at the Canberra Hospital. Letters are then allocated to participating surgeons containing the concealed treatment allocation. In this way the surgeon cannot influence the type of intervention; and the participants, clinical and research staff are blinded.

### Intervention

A fellowship trained orthopaedic surgeon with subspecialist hand surgery training will undertake the initial patient assessment and perform the surgery. All surgeons are experienced and familiar with both treatments.

Procedures are performed under general anaesthesia with antibiotic prophylaxis and the use of a tourniquet. A dorsal approach with full thickness skin flaps is used and the interval between the 3rd and 4th compartment is developed. In cases of minimal bone loss, local bone graft is used; in cases of advanced bone loss, cortico-cancellous bone graft is obtained from the ipsilateral iliac crest. If the distal radioulnar joint is arthritic, it is resected and used as bone graft. A dorsal capsulotomy is performed to expose the radiocarpal and midcarpal joint and a posterior interosseous nerve neurectomy is performed.

### Treatment a: Total wrist arthrodesis without CMCJ arthrodesis and non-bridging plate

Care is taken at this point not to damage the CMCJ or joint capsule which is identified by fine bore needle under fluoroscopy. After thorough decortication of the radiocarpal and midcarpal joints the Medartis 2.5 TriLock Wrist Fusion without arthrodesis of the carpometacarpal joint (Medartis, [name]) is applied according to manufactures instructions and intra-operative imaging is obtained to ensure correct placement.

### Treatment B: Total wrist arthrodesis with CMCJ arthrodesis and bridging plate

In addition to preparing the radiocarpal and midcarpal joints, the third CMCJ is prepared for arthrodesis. The third metacarpal is marked to ensure correct rotation and a Synthes-DePuy 2.7/3.5 mm stainless steel plate (Synthes-DePuy, [name]) is secured and intra-operative imaging is undertaken to confirm correct placement.

For both interventions, bone graft if used, is packed around the decorticated carpal bones. Wounds are closed in layers and interrupted nylon suture is used for skin. The wrist is then placed in a well-padded short arm volar plaster slab. Post-operative rehabilitation is standardised with immediate motion of the shoulder, elbow and fingers. At 2 weeks, participant wounds are checked, and they are supplied with a removable thermoplastic splint.

### Outcome assessment

A timeline for assessment is given in Fig. 1. Surgeons will record peri-operative complications and union on a standardised form. In each outpatient department a blinded physiotherapist will ensure post-operative assessment is completed at 1, 2 and 5 years. Patients will undergo assessment with DASH, PRWE, report pain, satisfaction and record perceived problems or complications.

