### Radiological evaluation

Routine x-ray and pre-operative CT will be used to assess the integrity of the CMCJ. Intraoperatively fluoroscopy will be used by the surgeon to assess hardware placement, screw length and position, and alignment and rotation of the hand.

Union of the radiocarpal, midcarpal and carpometacarpal joint will be assessed by an independent specialist radiologist at 4–6 months following TWA and be defined as the presence of bridging bony trabeculae.

Non-union will be defined as the absence of bridging trabeculae, with no documented interval change over a 3-month period.

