### Data collection

Data will be collected prior to surgery and in the post-operative period by the treating surgeon and at 1,2 and 5 years by blinded subspecialised hand physiotherapists, using standardised data forms (see additional files). These forms will be in locked a filing cabinet.

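### The operating surgeon, who knows the arm, records part of the 12-month primary outcome although clinical staff are said to be blinded, and the source that settles union is unclear

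*Protocol article*

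**What the plan says.** **On who is blinded.** The Background section says the study "is a single centre, multi-surgeon triple blinded randomised trial". Randomisation and blinding adds: "In this way the surgeon cannot influence the type of intervention; and the participants, clinical and research staff are blinded". Data management and Statistical analysis describe the data compiler and the statistician as blinded. Outcome assessment and Data collection describe the physiotherapists as blinded.

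**On who knows the arm.** Randomisation and blinding also says: "Letters are then allocated to participating surgeons containing the concealed treatment allocation". Under Intervention, the surgeon "will undertake the initial patient assessment and perform the surgery". The sections on Treatment A and Treatment B give different plates and different joint preparation.

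**On who records the outcome.** The primary outcome is complication within 12 months, as listed in Table 2, with non-union read from CT. Outcome assessment says "Surgeons will record peri-operative complications and union on a standardised form", and Data collection says "Data will be collected prior to surgery and in the post-operative period by the treating surgeon". The physiotherapists collect data at 1, 2 and 5 years, and patients report perceived problems at those visits.

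**On union.** Radiological evaluation says: "Union of the radiocarpal, midcarpal and carpometacarpal joint will be assessed by an independent specialist radiologist at 4–6 months following TWA".

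**The concern.** The person who chooses whether and how to write down a complication during most of the primary window knows which operation was done. For events such as hardware breakage or tendon rupture this matters little. For four Table 2 items it can matter: tendon irritation counts only if treated, superficial infection is defined by antibiotic treatment alone, nerve injury includes cases managed without operation, and there is an open category for other events. If surgeons look harder for trouble, or write it down more readily, in one arm, the primary odds ratio shifts. Recruiting more patients would not remove that shift.

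A report that repeats the general claim about clinical staff would also lead readers to assume a protection that part of the primary outcome does not have. Finally, non-union is a component of the primary outcome, and the article names the surgeon in one place and the radiologist in another without saying whose finding counts.

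**Working it through.** **Step 1: does the recorder know the arm?** Randomisation and blinding sends the allocation to the surgeon. Intervention has the surgeon operate. The treatment sections prescribe a non-spanning plate without preparation of the carpometacarpal joint (CMCJ) in one arm, and a spanning plate with the third CMCJ prepared in the other. The surgeon therefore knows the arm.

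**Step 2: does that person record primary-outcome data?** Outcome assessment covers peri-operative complications and union. Data collection widens this to the post-operative period. Both fall within the 12-month window.

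**Step 3: what blinded cover is there?** The first visit assigned to the physiotherapist is at 1 year, the end of the window. Problems reported by blinded patients are recorded there. The article gives no rule for combining these with the surgeon's form and describes no blinded adjudication.

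**Step 4: union.** Outcome assessment has surgeons record it, Primary outcome says non-union is assessed by CT, and Radiological evaluation has an independent radiologist assess union at 4–6 months. Non-union also requires no interval change over 3 months, which a single reading cannot show. The radiologist is called independent, not blinded, and can be expected to see the plate on CT.

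**Step 5: illustration of what differential recording could do.** The article gives no event rates, so its figure of 120 participants cannot be reproduced, and every rate below is an assumption.

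- Evaluable per arm: 120 / 2 = 60, and 60 × (1 − 0.20) = 48.
- Assumed true risk: 30% in both arms. Assumed capture: 95% in one arm, 70% or 80% in the other.
- Observed risk = true risk × capture: p = 0.30 × 0.95 = 0.285, against q = 0.30 × 0.70 = 0.210 or q = 0.30 × 0.80 = 0.240.
- Odds ratio = [q/(1 − q)] / [p/(1 − p)]: 0.2658 / 0.3986 = 0.67, or 0.3158 / 0.3986 = 0.79.
- False-positive rate of the unadjusted two-sided two-proportion test, with d = p − q, SE0 the pooled and SE1 the unpooled standard error: Φ[(d − 1.96·SE0)/SE1] + Φ[(−d − 1.96·SE0)/SE1].
  - 70% capture: d = 0.075, SE0 = 0.0881, SE1 = 0.0878, giving Φ(−1.113) + Φ(−2.822) = 13.5%.
  - 80% capture: d = 0.045, SE0 = 0.0898, SE1 = 0.0897, giving Φ(−1.461) + Φ(−2.464) = 7.9%.
- Fisher's exact test, summing the binomial probabilities of all rejecting tables at 48 per arm: 9.1% and 5.0%. The same sum with 30% in both arms and full capture is 2.9%, because that test is conservative.

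Sensitivity to the assumptions, with full capture in one arm, true risk of 20–40% in both, 48 per arm and the same normal-approximation formula:

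| Events missed in the other arm | Odds ratio | False-positive rate |
|---|---|---|
| 10% | 0.84–0.88 | 5.7–6.9% |
| 20% | 0.71–0.76 | 8.0–12.8% |
| 30% | 0.58–0.65 | 12.2–23.5% |

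**The case against.** An unblinded surgeon is unavoidable in this comparison, and this is a condensed article whose data forms sit in additional files that are not shown. That is fair. The point is therefore not that surgeons should be blinded, but that the article states both who is blind and who records, and the two do not fit together.

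A reader might infer more than the document supports:

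- **That the triple-blind label is false.** It can mean participant, physiotherapist and statistician, all of whom are named as blinded. The blinding sentence also mentions the surgeon apart from the staff it calls blinded. On that reading no surgeon blinding is claimed, but an unblinded person still records primary-outcome data.
- **That the two sections contradict each other on union.** One says record and the other says assess. A surgeon copying the radiologist's result onto the form would satisfy both. This is an ambiguity, not a contradiction.
- **That the surgeon supplies most of the primary data.** The text does not say so, and the blinded 1-year visit falls at the end of the window.
- **That the whole primary outcome is subjective.** Deep infection, fracture, CT non-union, hardware breakage and tendon rupture leave much less room for judgement, and complex regional pain syndrome has named criteria.
- **That the blinding of compiler and statistician fails.** The CMCJ is assessed for non-union only if it was arthrodesed, so a joint-level field could reveal the arm. Whether such a field reaches either person depends on forms and an analysis plan that are not shown.
- **That the illustration estimates the actual bias.** It applies one recording gap to every event, including CT-read ones where under-recording is least plausible.

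**Conclusion.** The concern holds in a limited form. The surgeon knows the arm and records complications and union in the peri-operative and post-operative period, so part of the 12-month primary outcome is recorded unblinded. The general statement about clinical staff does not fit with this. The blinded 1-year visit and patient reports give partial cover, with no rule on which source prevails. It is also unclear whether the surgeon's record or the radiologist's assessment determines union.

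The size and direction of any bias cannot be known from the document. The odds ratio of 0.67–0.79 and the false-positive rate of about 8–13.5% show only what a 15 to 25 percentage point gap in capture would do. They rest on an assumed 30% risk, a gap that affects all event types, 48 evaluable per arm and an unadjusted two-proportion test. With Fisher's exact test the rates are 5.0–9.1%.

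**What to change.** 1. **Non-union.** State that the independent radiologist's CT reading is the sole source, applied to whatever imaging is needed to meet the protocol's own 3-month interval definition, and that the surgeon form only transcribes it. Reconcile Outcome assessment, Primary outcome and Radiological evaluation accordingly.
2. **Other complications.** Keep the surgeon's contemporaneous record, but as dated facts: the event, the treatment given, any return to theatre. Have the blinded physiotherapist complete the Table 2 checklist with the patient at 1 year. Existing staff blinded to arm then classify primary-outcome status from both sources. The 1-year checklist should supplement the surgeon's record and not replace it, since a year's recall alone would miss resolved events such as a superficial infection.
3. **Analysis data, as a precaution.** Give the statistician the yes/no primary variable under coded arms, without joint-level CMCJ or plate fields, until the primary analysis is done.
4. **Wording.** Replace the general claim about clinical staff with the groups actually blinded: participant, physiotherapist and statistician. State that the surgeon is not blinded, and that the radiologist is independent but can be expected to see the plate.

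The cost is revised forms and wording, a slightly longer 1-year visit, and some time from existing blinded staff for classification. No new staff are needed and treatment does not change.
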